### Statistical analysis

Project 1 will compare the number of cloaked platelets, comparing healthy weight and overweight men using either the *t* test or the non-parametric Mann-Whitney test, depending on the normality of the data. Linear regression models will be used to test the association between obesity and extent of platelet cloaking, adjusting for potential confounders such as age, use of medications, and smoking. If the data are not normally distributed then a log transformation will be employed. In addition to comparing overweight and healthy weight men as a binary exposure, BMI will be modelled as an ordinal variable (<18.5, 18.5–24.9, 25.0–27.4, 27.5–29.9, 30+) and as a continuous variable and to test for linear trends with the log likelihood ratio test of nested models.

Project 2 will compare measurements of platelet cloaking at baseline and months 3 and 6 follow-up time points among men randomised to the exercise and control arms, in both the exposed (BMI ≥ 25) and non-exposed (BMI < 25) groups. Intention-to-treat analyses will use linear mixed-effect models to incorporate each biomarker for a given participant over time. BMI will also be stratified to look at potential effect modification. To estimate longitudinal changes in quality of life scores from baseline, the primary analysis will be carried out using a mixed-effects model for repeated measures.

Project 3 will examine the extent of the inflammatory infiltrate in diagnostic NCBs. All variables will be correlated with CTC numbers and platelet cloaking using basic descriptive statistics such as Pearson correlation coefficients for continuous variables and simple *t* tests for categorical variables. In the event of skewed distributions or sparse data, we will use non-parametric tests such as the Spearman correlation and Mann-Whitney. Moreover, a principal component analysis will be undertaken to estimate the proportion of variability in platelet cloaking and CTC number which is explained as a function of the obesity inflammatory biomarkers. The biomarkers will be modelled as principal components in the linear regression and adjusted for potential confounders such as age, smoking, and other factors.

Project 4: Generalized linear regression models will be used to examine whether obesity is associated with expression of each of the five markers in the tumour tissue, adjusting for potential confounders such as age and smoking status, as well as clinical features. Obesity will be dichotomised as BMI greater or less than 25, and we will also model BMI as a continuous variable and examine tests for trend. The expression of each marker will be assessed with respect to the extent of platelet cloaking (high, intermediate, and low). The categorisation of platelet cloaking as high, intermediate, and low is dependent on the proportion of CTCs with adherent platelets (high > 75%, intermediate 25–75%, low < 25%). A gene score will be created by ranking individuals across expression of each gene in tertiles, assigning points for each marker as lowest tertile = 0, middle tertile = 1, upper tertile = 2, and calculating a summary score.

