**Fig. 1 Fig1:**
[figure not shown]
Schematic of the four projects involved in the ExPeCT trial. *BMI* body mass index, *CTC* circulating tumour cell, *H&E* haematoxylin and eosin, *NK* natural killer, *TNF* tumour necrosis factor

Project 1: CTCs will be enumerated in the T0 samples. Adherent platelets will be quantified and compared between the exposed and non-exposed groups, and correlated with clinicopathological parameters.Project 2: The exercise group will undertake a regular supervised aerobic exercise programme, whereas the control group will not. T3 and T6 blood samples will be assessed for CTC numbers and platelet cloaking. Changes will be compared with the T0 sample, and between exposed and non-exposed, and exercise and control groups. Participants will complete a detailed questionnaire to assess QoL and other parameters at each visit.Project 3: Blood samples will be assessed for NK cell number and activation, markers of systemic inflammation, adipokines, and serum factors related to platelet activation. The prostate needle core biopsies (NCBs) will be examined microscopically for atrophy and inflammation by morphology and immunohistochemistry, with particular reference to NK cells. All variables will be correlated with platelet cloaking.Project 4: NCBs will be assessed for expression of an obesity-associated lethality gene signature (whose genes are known to play a role in obesity or platelet aggregation and coagulation), and correlated with platelet cloaking of CTCs.

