### Sample size

We will recruit 200 participants over the lifetime of the study, evenly divided between the exercise group and the control group. To calculate the power of the study, we used data from a previous study of ovarian cancer cell lines which showed approximately 2% platelet adhesion [21]. A standard deviation (SD) varying from 2% to 10% would enable us to detect a difference of platelet cloaking of between 0.79% and 3.9%. Research into this area is at an early stage and the clinical importance of specific incremental changes in the degree of platelet cloaking is as yet uncertain, but its elucidation is beyond the scope of this study.

With regard to the detection of changes in platelet cloaking with time, and taking the same assumptions regarding SD of platelet adhesion in PrCa CTCs as in project 1, we will be able to detect a change of 1.8% platelet cloaking between any two time points in the 100 participants in each of the exercise and the control groups, determined by paired *t* testing. A SD varying from 2% to 10% would enable us to detect a difference of platelet cloaking of between 0.56% and 2.8%. Generalised linear mixed models will be employed in order to account for the correlation between multiple measurements in the same experimental subject.

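### Project 2 describes the randomised comparison as change from T0 and does not condition the arm effect on T0 cloaking; doing so would gain efficiency at almost no cost

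*Protocol article*

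**What the plan says.** Under ExPeCT study design, the description of Project 2 sets the contrast for the follow-up samples: "Changes will be compared with the T0 sample, and between exposed and non-exposed, and exercise and control groups".

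Under Statistical analysis, Project 2 lists baseline with months 3 and 6 as the cloaking measurements to be compared between the randomised arms, within both BMI groups. The model is given in one sentence: "Intention-to-treat analyses will use linear mixed-effect models to incorporate each biomarker for a given participant over time". BMI appears there for subgroup comparison and effect modification. Quality of life is also framed as change; its mixed model for repeated measures is introduced with "To estimate longitudinal changes in quality of life scores from baseline". No fixed effects are listed for either model.

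The Sample size section gives the only numbers:

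- Size: "We will recruit 200 participants over the lifetime of the study, evenly divided between the exercise group and the control group".
- Two-group comparison, in the paragraph that the text later refers to as project 1: "A standard deviation (SD) varying from 2% to 10% would enable us to detect a difference of platelet cloaking of between 0.79% and 3.9" (per cent).
- Change over time, "taking the same assumptions regarding SD of platelet adhesion in PrCa CTCs as in project 1": a change "between any two time points in the 100 participants in each of the exercise and the control groups, determined by paired *t* testing", with the result "A SD varying from 2% to 10% would enable us to detect a difference of platelet cloaking of between 0.56% and 2.8" (per cent).

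The section states no alpha, power or T0-to-follow-up correlation, and no between-arm difference for Project 2.

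**The concern.** Cloaking is to be measured at T0 in each man, so the T0 value is available as a predictor of his T3 and T6 values. A plain difference in change subtracts the whole T0 reading, noise included. Adjustment subtracts only the part of T0 that predicts follow-up. In large samples it is never less precise than the change score, and at moderate correlation it is clearly more precise.

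At stake is the power of the one randomised test in the trial, whether exercise reduces cloaking. The planning SD for that endpoint is uncertain fivefold, from 2% to 10%, so precision that costs no recruitment is worth having.

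**Working it through.** **1. Reproduce the stated figures.** Alpha and power are not given. Two-sided 5% and 80% power reproduce the figures, with multiplier 1.960 + 0.842 = 2.8016.

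- Two groups of 100: 2.8016 × SD × √(2/100) gives 0.792 at SD 2% (stated 0.79) and 3.96 at SD 10% (stated 3.9).
- Paired, n = 100: 2.8016 × SD / √100 gives 0.560 at SD 2% and 2.80 at SD 10% (stated 0.56 and 2.8).

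**2. Infer a correlation.** The paired figures use the same SD range as the two-group figures. If that SD is the SD of a single reading, the SD of change has been set equal to it. The variance of change is 2(1-rho)σ², so 2(1-rho) = 1 and rho = 0.5. If the SD was instead meant as the SD of change, rho is undetermined. The value 0.5 is therefore an assumption, and a range is shown in step 4.

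**3. Variance of the arm contrast at one visit** (n = 100 per arm, complete data, equal variance at each visit):

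- Difference in change: 2(1-rho) × σ² × 2/n
- Adjusted for T0: (1-rho²) × σ² × 2/n
- Ratio of adjusted to change: (1+rho)/2, which is 0.75 at rho = 0.5

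**4. Power at a fixed difference.** Take 2.8016 × √0.02 = 0.396 SD, which the change contrast detects with 80% power at rho = 0.5.

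- Change, rho 0.5: SE = √(1.00 × 0.02) = 0.1414; Φ(0.396/0.1414 - 1.96) = 80.0%
- Adjusted, rho 0.5: SE = √(0.75 × 0.02) = 0.1225; Φ(0.396/0.1225 - 1.96) = 89.9%

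| rho | Change from T0 | Adjusted for T0 | Gain (percentage points) |
|---|---|---|---|
| 0.3 | 65.8% | 83.6% | 18 |
| 0.4 | 72.5% | 86.4% | 14 |
| 0.5 | 80.0% | 89.9% | 10 |
| 0.6 | 87.9% | 93.8% | 6 |
| 0.7 | 95.1% | 97.5% | 2 |

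**5. In the article's units, rho = 0.5.** A between-arm difference of 0.79 at SD 2% has 79.8% power as change and 89.7% adjusted. A difference of 3.9 at SD 10% has 78.7% and 89.0%. Both differences are borrowed from the two-group calculation, since none is stated for Project 2. The difference detectable with 80% power falls from 0.396 to 2.8016 × √0.015 = 0.343 SD, that is from 0.79 to 0.69 at SD 2% and from 3.96 to 3.43 at SD 10%.

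**6. Does keeping T0 as an outcome lose the gain?** Generalised least squares was applied to a three-visit model with equal correlation between visits. With separate T0 means per arm, power at one visit equals that of the change score (80.0% at rho 0.5). With one common T0 mean it equals that of the adjusted analysis (89.9%). If T3 and T6 are averaged at rho 0.5, the figures are 89.9% and 97.7%, a gain of 8 percentage points.

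**The case against.** The strongest reply is that the article does not specify the model. It describes itself as excerpts of a longer protocol, and a list of fixed effects is what such an article usually leaves to the full protocol or analysis plan. A mixed model over T0, T3 and T6 could be one with a common T0 mean, which loses nothing. This stands. What remains is that the contrast written down is change from T0 between arms, with nothing said about conditioning on T0.

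Several stronger readings are tempting, and the document does not support them:

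- **That the plan loses 10 percentage points of power on its own inputs.** Rho = 0.5, alpha and power are all inferred. The section also quotes a detectable change of 1.8%, which needs an SD of 1.8 × 10/2.8016 = 6.4%, a value it never gives, so it is a weak basis for inferring a correlation. The gain shrinks quickly as rho rises.
- **That treating T0 as a repeated outcome itself costs power.** It does so only with separate T0 means and the effect read as the difference in change.
- **That the comparison is biased.** Under randomisation the change contrast is unbiased and keeps its type I error. Regression to the mean matters only conditionally, given a chance T0 imbalance.
- **That the quality-of-life model omits the baseline score.** The text does not say so.
- **That Project 2 is inconsistent because the other projects name covariates.** Those are confounders in observational comparisons, and a randomised comparison does not need them for validity.
- **That country must be in the model.** The article describes no stratification of the randomisation by country, so this would be preference.

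**Conclusion.** The point holds as one of efficiency and clarity, not of validity. As described, the randomised contrast is change from T0, and conditioning on T0 cloaking is not stated. If the model has separate T0 means and the effect is the difference in change, adjustment multiplies the variance by (1+rho)/2. At rho = 0.5 that is a 25% reduction, or power of about 90% in place of 80% at 0.396 SD. Over rho 0.3 to 0.7 the gain at that difference runs from about 18 to 2 percentage points. This rests on two-sided 5%, 100 men per arm with complete data, equal variances across visits, and an assumed rho. If the full protocol or analysis plan already adjusts for T0 or uses a common T0 mean, only the wording needs attention.

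**What to change.** State in Project 2 that the exercise-control difference at T3 and at T6 is estimated in one of two ways:

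- a mixed model for T3 and T6 cloaking with T0 cloaking as a covariate, with its own slope at each visit; or
- a mixed model with T0, T3 and T6 as outcomes and one common T0 mean for both arms.

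In either case include BMI group (≥ 25 v < 25) as a fixed effect. The trial's own hypothesis links it to cloaking, though no gain has been computed for it here. Use the same approach for FACT-P and the other quality-of-life scores.

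The cost is a sentence or two of analysis text, with no new data, visits or participants. The covariate version drops men with no T0 reading; the common-mean version avoids this.

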## Methods and design

### ExPeCT study objectives

The overarching hypothesis is that enhanced platelet cloaking of CTCs in obese men with prostate cancer, due to increased systemic inflammation, is a mechanism underlying worse prognosis of cancer in these patients.

The aim is to test the following four hypotheses, dividing the experimental and analytical work into four separate projects:Platelet cloaking of circulating PrCa tumour cells is more prominent in men with obesity than without.Regular exercise can ameliorate platelet cloaking.The degree of platelet cloaking varies with levels of systemic and primary tumour inflammation and coagulability.Expression of an obesity-associated lethality gene signature leads to variation in platelet cloaking.

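### Project 4's cloaking bands at 25% and 75% do not fit the sample-size assumptions (about 2%, SD 2 to 10 points) if both describe the same quantity

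*Protocol article*

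**What the plan says.** The fourth hypothesis in the ExPeCT study objectives is "Expression of an obesity-associated lethality gene signature leads to variation in platelet cloaking". For Project 4, the Statistical analysis section assesses each marker against cloaking classed as high, intermediate or low. The class depends on what share of a man's CTCs have platelets attached: "high > 75%, intermediate 25–75%, low < 25" (percent). It gives no reason for the cut-points and no fallback if a class is empty.

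The Sample size section takes its planning value from "a previous study of ovarian cancer cell lines which showed approximately 2% platelet adhesion". It continues: "A standard deviation (SD) varying from 2% to 10% would enable us to detect a difference of platelet cloaking of between 0.79% and 3.9" (percent). For change over time within a group of 100 it gives a "difference of platelet cloaking of between 0.56% and 2.8" (percent).

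Two other places matter. The Project 4 summary in the ExPeCT study design section says that biopsy gene expression will be correlated with cloaking, and mentions no bands. The Primary study endpoint section counts the CTCs with platelets attached and also estimates the number of platelets per cell.

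**The concern.** The Sample size section works on a scale where the typical value is about 2% and men differ by 2 to 10 points. Project 4 uses a scale where men are expected to spread across cut-points at 25% and 75%. Both sections call the quantity platelet cloaking and express it in percent.

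One of two things follows. If the scale is the same, two of the three bands may be almost empty and the banded comparison of gene expression would tell the reader very little. If the scale differs, the bands may be usable, but the detectable differences quoted for the primary endpoint are not differences in the proportion of cloaked CTCs. The article does not say which case applies.

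**Working it through.** **Inputs.** From the Sample size section: 200 men, 100 per group; planning value about 2%; SD 2 to 10 points. From the Statistical analysis section: cut-points at 25% and 75%. Assumed, because the article gives neither: two-sided 5% and 80% power, so the multiplier is 1.960 + 0.842 = 2.802. Gene data are taken to be available for all 200 men.

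**1. The plan's own figures.** Two groups of 100: 2.802 × SD × √(2/100).
- SD 2: 0.79 (stated 0.79).
- SD 10: 3.96 (stated 3.9, at which power is 78.7%).

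Paired, n = 100: 2.802 × SD / √100 gives 0.56 and 2.80, as stated. The figures are reproduced. They use only the SD and n; the 2% does not enter.

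**2. Same scale, mean 2%.** For any non-negative quantity, the share at or above a threshold is at most mean/threshold (Markov's inequality).
- At or above 25%: 2/25 = 8%, or 16 of 200.
- Above 75%: 2/75 = 2.7%, or about 5 of 200.

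So at least 92% are expected in the low band. Specific distributions with mean 2% give fewer men outside it:

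| SD (points) | Men of 200 at or above 25% | Men of 200 above 75% |
|---|---|---|
| 2 | 0 to 0.06 | 0 |
| 5 | 0 to 2.1 | 0 to 0.1 |
| 10 | 2.1 (normal, lognormal) to 5.6 (beta) | 0 to 1.3 |

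(Ranges over normal, lognormal, gamma and beta.)

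**3. Same scale, mean left open.** Let shares p and q of men be low and high. These men differ by at least 75 − 25 = 50 points, so the variance is at least 50² × pq/(p+q) = 2500 × pq/(p+q). For a given smaller share s, this is least when p = q = s, where it equals 1250 × s. With SD at most 10, 1250 × s ≤ 100, so s ≤ 8% (16 of 200), whatever the mean.

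**4. What the banded comparison could detect,** in SDs of marker expression.
- Low versus the rest, m men outside low: 2.802 × √(1/m + 1/(200 − m)) gives 1.99 for m = 2, 1.27 for m = 5 and 0.73 for m = 16.
- Low versus high with SD at most 10 and any mean: step 3 gives 1/p + 1/q ≥ 2500/100 = 25, so the detectable difference is at least 2.802 × √(25/200) = 0.99.
- For comparison, two tertiles of observed cloaking (67 men each): 2.802 × √(2/67) = 0.48. Continuous cloaking: a correlation of tanh(2.802/√197) = 0.20.

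**5. Different scale.** Equal thirds across the bands need a variance of at least 2500 × (1/9)/(2/3) = 416.7, an SD of at least 20.4 points. The detectable difference between two groups of 100 is then at least 2.802 × 20.4 × √0.02 = 8.1 points, against the stated maximum of 3.9. As a further illustration, an assumed beta distribution with mean 50% and SD 30 points puts 27%, 47% and 27% of men in the bands; the detectable difference is 2.802 × 30 × √0.02 = 11.9 points.

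**The case against.** The strongest reply is that the 2% is an adhesion figure from cell lines, borrowed because nothing better was available. The article never equates it with each man's share of cloaked CTCs, and the detectable differences do not depend on it. Step 2 is therefore conditional. This stands, and it rules out reading the plan as showing that almost every man will be low. It does not remove the mismatch: step 3 uses only the SD range, which the Sample size section applies to prostate CTCs and reports as cloaking.

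A reader might also infer that hypothesis 4 cannot be tested, or that it rests on the bands alone. The documents do not support that. The ExPeCT study design section plans an unbanded correlation, and the Primary study endpoint section collects the counts it needs.

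Nor is the banded analysis empty in every case. With 16 men outside low, the detectable difference is 0.73 SD, which is weak but not nil. If the mean lay near a cut-point, two bands could be well filled: an assumed beta with mean 30% and SD 10 points gives 33% low and 67% intermediate. What the SD range rules out is a well-filled low band together with a well-filled high band.

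Finally, gene expression is a secondary endpoint, and the stated cloaking comparisons in Projects 1 and 2 do not use the bands. That limits the consequence of the first reading, but not of the second, which touches the primary endpoint's sample-size basis.

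**Conclusion.** The bands and the planning figures do not fit if they describe the same quantity. With a mean of 2%, at most 16 of 200 men are expected outside the low band and about 5 at most in the high band, so the three-band comparison would be nearly uninformative. With the mean left open and an SD of at most 10 points, the smaller of the low and high bands holds at most 16 of 200, and a low-versus-high comparison could detect no difference smaller than about 1 SD of expression.

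If the quantities differ, the bands may be populated, but 0.79% to 3.9% is then not a statement about the cloaked proportion; about 8 points is the corresponding figure if the bands were to hold equal thirds.

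It would be too strong to say that the two sections cannot both hold: they can, on different scales, but the article then needs to say so. Confidence is moderate, because the 2% comes from cell lines and its scale cannot be checked from the article. The power arithmetic assumes two-sided 5% and 80%, which reproduce the stated figures closely.

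**What to change.** 1. In Project 4, relate each of the five genes and the gene score to the unbanded cloaked proportion (cloaked out of total CTCs per man). Use rank correlation, or a regression that allows for overdispersion and small CTC counts. This agrees with the correlation already named in the ExPeCT study design section. The choice of model and covariates is for the trial team.
2. Keep the 25% and 75% bands for description only.
3. Define platelet cloaking on one scale in the Sample size and Statistical analysis sections. Say whether the 2% and the SD range refer to the per-man proportion, and restate the detectable differences if the SD range changes.

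The cost is minor rewording; the counts are already collected. One limit should be stated: if 2% did apply and men had few CTCs (say 5 each), only 1 − 0.98⁵ = about 10% of men would show any cloaked cell, so the unbanded analysis would also be sparse. It would still discard less information than the bands.

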### Ethics and research governance

The study protocol and other documentation have been approved by NRES Committee London—Camden & Islington (REC reference 14/LO/1859), The Mater Misericordia Hospital Research Ethics Committee, Dublin (REC reference: 1/378/1760), Beaumont Hospital Ethics (Medical Research) Committee, Dublin (REC Reference 15/73), SJH/AMNCH Research Ethics Committee, Dublin (REC Reference: 2014-11 List 41 (6)) and St Luke’s Radiation Oncology Network, Dublin (REC Number not assigned. Trial referred to as ICORG 15-21 (sponsorship identifier)).

Cancer Trials Ireland is the sponsor for the Irish sites on this study (Protocol Number CTRIAL-IE (ICORG) 15-21).

